**Supplementary data**

**Cancer prediction in Lambert-Eaton myasthenic syndrome in a prospective cohort**

**Supplementary figure 1.** Receiver operating characteristic curve for DELTA-P scores in the prospective LEMS cohort (n=87)(AUC=82.5%).

**LIST OF ABBREVIATIONS AND RELEVANT DEFINITIONS**

| **CCMO** | **Central Committee on Research Involving Human Subjects; in Dutch: Centrale Commissie Mensgebonden Onderzoek** |
| --- | --- |
| **CMAP** | **Compound Muscle Action Potential** |
| **DC** | **Dendritic Cells** |
| **EMG** | **Electromyography** |
| **HLA** | **Human Leukocyte Antigen** |
| **KIR** | **Killer immunoglobulin-like receptor** |
| **LEMS** | **Lambert-Eaton Myasthenic Syndrome** |
| **LUMC** | **Leiden University Medical Center** |
| **METC** | **Medical research ethics committee (MREC); in Dutch: medisch ethische toetsing commissie (METC)** |
| **MG** | **Myasthenia Gravis** |
| **PBMC** | **Peripheral Blood Mononuclear Cell** |
| **SCLC** | **Small Cell Lung Cancer** |
| **Sponsor** | **The sponsor is the party that commissions the organisation or performance of the research, for example a pharmaceutical**  **company, academic hospital, scientific organisation or investigator. A party that provides funding for a study but does not commission it is not regarded as the sponsor, but referred to as a subsidising party.** |
| **VGCC** | **Voltage-Gated Calcium Channels** |
| **WMO** | **Medical Research Involving Human Subjects Act (in Dutch: Wet Medisch-wetenschappelijk Onderzoek met Mensen** |

**SUMMARY**

**Rationale:** A detailed description of clinical characteristics and disease course of patients with Lambert-Eaton myasthenic syndrome (LEMS) will enable earlier diagnosis and treatment of this rare, disabling, but well-treatable, neuromuscular disorder and the associated tumour. This study will provide detailed knowledge about the immune response against voltage-gated calcium channels and the small cell lung cancer (SCLC) in patients with LEMS. This is essential for the development of future therapeutical interventions or immune-mediated therapies.

**Objective**:

- To study the clinical characteristics and disease course of patients with LEMS with or without SCLC.
- To identify the characteristics of the humoral or cellular immune response that are associated with the prolonged survival of patients with SCLC and LEMS.

**Study design:** Single center prospective study

**Study population:** Patients with Lambert-Eaton myasthenic syndrome or SCLC.

**Main study parameters/endpoints:** Description of epidemiology, clinical characteristics and disease course in LEMS patients. Prediction of presence of an underlying SCLC in LEMS patients. Comparison of the humoral and cellular immune response in LEMS patients and SCLC patients with and without LEMS.

**Nature and extent of the burden and risks associated with participation, benefit and group relatedness:** Patient burden and risk in this study will be minimal and mostly almost completely limited to the period shortly after inclusion. If a patient participates in all elements of the study this will include:

- detailed history and physical examination

- electromyogram to determine the severity of the LEMS

- blood donation. We will draw 90 mL at inclusion and up to 50 mL at follow-up for selected patients with SCLC.

Personal benefit would be the contact with the clinical researchers experienced in the treatment of this rare disorder, with the opportunity to be completely informed on all aspects of the disease and get detailed therapeutical advice. At a group level the results will contribute to improved understanding of the pathogenesis, and possibly improved therapies.

# INTRODUCTION AND RATIONALE

LEMS is an antibody-mediated autoimmune disorder characterised by proximal muscle weakness, loss of tendon reflexes and autonomic dysfunction.

*Clinical features*

It can occur at all ages and affects both men and women. LEMS is associated with pathogenic antibodies against the presynaptic P/Q-type voltage-gated calcium channel (VGCC) in 90% of patients. In about 50-60% of patients small cell lung cancer (SCLC) is detected.^1^

LEMS usually presents with progressive proximal leg weakness, which occurs in virtually all patients during the course of the disease. As in myasthenia gravis (MG), weakness usually progresses to other muscle groups. These include the arms, feet and oculobulbar muscles causing ptosis, diplopia and dysarthria. However, in LEMS weakness generally spreads in caudocranial direction, while in myasthenia gravis it usually spreads in the opposite direction.^2^ In contrast to MG, symptoms of autonomic dysfunction occur in 80-90% and include dry mouth and eyes, erectile dysfunction, constipation and blurred vision. Although rare, respiratory failure can occur and is described as presenting symptom in single cases.

*Diagnosis of LEMS*

Diagnosis of LEMS usually precedes diagnosis of SCLC by several months, thus prompting vigorous tumour screening.^3^ The presence of an underlying SCLC causing LEMS is of uttermost importance and therefore discriminating SCLC-related LEMS from non-tumour (NT)-LEMS as well. Although comparable at first sight, SCLC-LEMS is generally a more rapidly progressive and severe disease, with weakness spreading more quickly.

*Pathogenesis*

The pathogenesis of LEMS is known in detail. IgG antibodies to presynaptic P/Q-type voltage gated calcium channels cause muscle weakness and autonomic dysfunction by interfering with Ca2+-dependent neurotransmitter release.^1, 4^ The target of these antibodies, the P/Q-type VGCC, is present at the neuromuscular junction as well as in SCLC tumour cells.^5^ These antibodies can block Ca2+ influx through voltage-gated calcium channels in SCLC cell lines.^4^ It is likely that that an immune reaction against antigenic determinants on the tumour's surface triggers autoantibody production, and these antibodies cross-react with VGCC on the nerve terminals and cause neurological disease. The detailed insight into the pathophysiology and interaction between LEMS and SCLC make LEMS an excellent candidate to study mechanisms of both general autoimmunity and tumour immunology.

*LEMS and small cell lung cancer*

Lung cancer is the number one cause of cancer-related death in both women and men. Small cell lung cancer (SCLC) accounts for approximately 13-16% of pulmonary tumours and is an aggressive disease with a median survival of only 10 months.^6-8^ Only modest improvements have been seen in survival over the last 30 years.^6^ In the Netherlands each year about 1700 patients are diagnosed with a SCLC. It is a very immunogenic tumour, frequently eliciting antibodies against tumour antigens. Many of the SCLC-associated antigens are also present in the nervous system, due to the neuro-endocrine origins of SCLC. Several tumour related neurological autoimmune syndromes have been described in SCLC patients. The best defined of these paraneoplastic disorders are the Lambert-Eaton myasthenic syndrome (LEMS) and the anti-Hu syndrome.

A profound effect on survival has been observed in SCLC patients with a paraneoplastic neurological disorder. Supporting a role for an effective anti-tumour immune response are reports of spontaneous remission of a proven lung tumour.^9, 10^ The most impressive prolonged survival has been observed in patients with LEMS. This effect has been shown both in our cohort as well as an independent British cohort. Three studies report a significantly prolonged median survival of 17, 20 or 24 months, compared to 10 months in the control groups of SCLC patients.^11-13^ In our cohort, three year survival was improved from 2% to 33%.^14^ This suggests a role for the immune response in controlling the tumour growth. Besides an antibody response, SCLC is an important immunological target for a cellular immune response as well. Previous studies have described the role of tumour-infiltrating lymphocytes and macrophages in immune responses to several tumour types.^15-17^ In SCLC, abundant presence of these cell types infiltrating the tumour has been associated with a favourable disease course.^15^ Overall, both cellular and humoral immunity seem to differ in SCLC patients with and without paraneoplastic syndromes, reflecting a more tumour-rejecting type of immune response in patients with paraneoplastic neurological disease.^15, 18^ However, the mechanism by which these immune responses can influence tumour growth remain unclear.

*Role for genetic variation*

Genetic variation in several genes has been associated with variation in susceptibility to and survival of SCLC in several studies.^19, 20^ Gene groups responsible for immune regulation such as human leukocyte antigen (HLA) and Killer immunoglobulin-like receptor (KIR) have also been shown to differ in occurrence in both SCLC as well as the associated anti-Hu paraneoplastic syndrome.^21, 22^ Future candidate gene and association studies could further indicate the role for specific gene markers which determine susceptibility and prognosis.

*Treatment*

The treatment consists of symptomatic treatment (3,4-diaminopyridine or pyridostigmine), prompt tumour treatment or immunosuppression, including prednisolone, azathioprine or cyclosporine.^23^ Current treatment is able to control signs and symptoms, but often at the cost of more or less severe side-effects of immunosuppressive or lung cancer treatment. The long-term prognosis of non-tumour LEMS regarding life expectancy is good, in contrast to the LEMS patients with SCLC. The presence of LEMS in a patient with SCLC improves survival, but as discussed above only one third of the patients survives beyond 3 years.^14^

Further insight into immune response and improved tumour treatment would be very helpful.

This study protocol is an extension of the previous protocol titled “Klinische manifestaties, pathogenese en behandeling van het Lambert-Eaton myastheen syndroom” (protocol number P181/98) which has previously been approved by the METC. Our research group has collected and characterized 120 patients with LEMS, which now is the largest well-defined cohort of LEMS patients worldwide.

*Preliminary results*

Our studies over the last years have focussed on the clinical manifestations and treatment as well as pathogenesis of LEMS and interaction with SCLC. These have led to several publications in high-ranking journals, like Journal of Clinical Oncology or Lancet Neurology.^1, 24, 25^

We were first to describe antibodies to the VGCC-beta subunit in patients with LEMS and detected the HLA association of LEMS.^26, 27^ Non-tumour LEMS is strongly associated with the highly conserved HLA-8.1 haplotype, indicating a hereditary genuine risk for developing an autoimmune disease. SCLC-LEMS patients carry HLA-types not different from the general population, suggesting that SCLC tumour cells actually elicit the autoimmune reaction irrespective of the underlying HLA haplotype.

In collaboration with all university hospitals and several larger non-university hospitals in the Netherlands we now have collected information on 120 patients with LEMS, with or without SCLC. Our recent projects on LEMS have resulted in a detailed description of the epidemiology of LEMS.^1, 28^ We have described the clinical manifestations in multiple publications.^2, 29, 30^ We have conducted a randomized, double-blind, crossover study showing the efficacy of 3,4-diaminopyridine compared to pyridostigmine and placebo.^31^

About half of the Dutch LEMS patients develop a SCLC. We have shown a prolonged survival in SCLC patients with LEMS compared to patients with SCLC alone.^11, 14^ We also evaluated the screening for SCLC in patients with LEMS and showed that a SCLC can be found in 96% of SCLC-LEMS patients within a year of the diagnosis of LEMS. We demonstrated that a CT-thorax is superior to X-thorax to detect a SCLC in LEMS (92% vs. 51%).^3^ Detailed analysis of clinical and demographic characteristics from two independent patient cohorts has led us to develop the DELTA-P score.^25^ This prediction model has provided for a simple clinical tool to indicate the presence of SCLC early in the course of the disease and can be used to guide tumour screening in individual patients.

In collaboration with Barcelona, we described SOX1 antibodies to be specific for LEMS patients with SCLC.^32, 33^ To further study the relationship with SCLC, a collaboration with the laboratory of prof [name] has been started. His lab has extensive experience with several in vitro tumour models and the study of T cells, macrophages, cytokines and their interactions.^34-36^ This setup is readily available to be applied to SCLC cell lines and patient derived mononuclear blood cells. Subsets of macrophages and T cells in several solid tumours were defined that correlate with different anti-tumour immune responses.

*Rationale*

We will continue to study clinical characteristics and disease course of LEMS patients in the Netherlands. Further characterisation of this rare disease will increase recognition of corresponding symptoms, thus enabling earlier diagnosis.

This study will also provide detailed knowledge about the immune response against SCLC in LEMS patients. We will classify SCLC patients with and without LEMS according to immunological profile and give insight into the cellular immune response. This could elucidate pathways to future immune-based therapeutic strategies aimed at SCLC.

In addition, analysis of the anti-tumour immune response will aid our understanding of the generation of an autoimmune neurological disease from this immune reaction. Especially in LEMS, the strong tumour association and detailed insight into the pathophysiology make this disease an ideal candidate to study mechanisms of general autoimmunity as well as tumour immunology.

# OBJECTIVES

*Main objective:*

To understand the pathophysiology of the immune response against VGCC in tumour- and non-tumour related LEMS.

*Specific objectives:*

1. To describe in detail the epidemiology, clinical characteristics (including imaging studies) and disease course of the Lambert-Eaton myasthenic syndrome with or without SCLC.
2. To prospectively test the ability of the DELTA-P score to predict the presence of an underlying SCLC in LEMS patients.
3. To study biomarkers in the peripheral blood of patients with LEMS, LEMS and SCLC, or SCLC only.
4. To study the humoral and cellular aspects of the tumour immune response in patients with SCLC and LEMS.

# STUDY DESIGN

This study will be a single center prospective study. An overview of procedures is further detailed in section 5.

Duration: Starting spring 2013

Setting: The study will be conducted at LUMC, Leiden, the Netherlands. Our neuromuscular outpatient clinic has longstanding expertise in diagnosing and treating LEMS patients. Patients with this diagnosis are referred to our center on a regular basis for second opinion. All academic centers in the Netherlands will also cooperate in referring newly diagnosed LEMS patients

We will include 50 consecutive LEMS-negative SCLC patients diagnosed in the LUMC as a control group for immunological studies.

# STUDY POPULATION

## Population (base)

We will aim to include all patients diagnosed with Lambert-Eaton myasthenic syndrome in the Netherlands.

Inclusion of patients with LEMS can occur by 3 different methods.

1. Newly diagnosed LEMS patients in the neuromuscular outpatient clinic of the LUMC
2. LEMS patients diagnosed elsewhere. All academic centres and a large number of neurologists from peripheral centres in the Netherlands have been cooperating over the years in referring newly diagnosed LEMS patients for second opinion and therapy advice.
3. All patients tested positive for VGCC antibodies in the LUMC (laboratory dr. ir. [name]) and the Erasmus MC (laboratory prof. dr. [name]). We will contact the physicians of patients positive for VGCC antibodies and ask them to inform their patients of our study. A positive test VGCC antibodies is highly predictive for the presence of clinically relevant LEMS. (attachment E3.1, E3.2).

Inclusion of SCLC patients

1. The department of pulmonology will refer all patients diagnosed with SCLC.

For some objectives (imaging studies, biopsies), retrospective patients in the LUMC will be included.

## Inclusion criteria

*Diagnosis of LEMS*
Criterion 1 and 2 or 1 and 3 have to be fulfilled

1. Clinical features consistent with LEMS (proximal muscle weakness, reduced tendon reflexes, autonomic symptoms)
2. Abnormalities upon repetitive nerve stimulation (decrement of CMAP amplitude and/or increment after voluntary contraction or high frequency stimulation)
3. Presence of VGCC antibodies

*Diagnosis of SCLC*

Definitive diagnosis of SCLC based on pathology results (either cytology or histology).

## Exclusion criteria

- Age < 18 years
- Unable to give informed consent

# METHODS

## Study parameters/endpoints

Parameters/endpoints for each of the objectives stated in chapter 3:

1. Epidemiology, clinical characteristics and disease course of LEMS with/without SCLC

*Introduction*

Many of our previous studies have focussed on clinical characteristics of LEMS patients. Based on the previous years, we expect to include 4-6 LEMS patients per year. For most clinical characteristics and the disease course, we will not define specific endpoints in advance.

We will specifically focus on lung imaging studies to determine tumour size and growth upon diagnosis in SCLC-LEMS patients compared to SCLC only. A prolonged survival has been observed in SCLC-LEMS patients, as well as increased tumour infiltration by macrophages.^16^ Lung tumours in LEMS are also frequently present in mediastinal lymph nodes only. Imaging studies in these patients might therefore show a difference in tumour size and growth as well as distribution.

*Hypothesis*

Lung tumours in SCLC-LEMS patients are smaller on average and grow at a slower rate compared to tumours in SCLC patients without LEMS.

*Endpoints*

Tumour size and growth rate upon follow-up.

Distribution of metastases.

1. To prospectively test the ability of the DELTA-P score to predict the presence of an underlying SCLC in LEMS patients.

*Introduction*

Detailed analysis of clinical and demographic characteristics from two independent patient cohorts has led us to develop the DELTA-P score.^25^ This prediction model has provided for a simple clinical tool to indicate the presence of SCLC early in the course of the disease and can be used to guide tumour screening in individual patients. This model has not yet been investigated prospectively.

*Hypothesis*

The DELTA-P score accurately predicts presence of SCLC in newly diagnosed LEMS patients.

*Endpoints*

Clinical characteristics necessary for DELTA-P score.

Diagnosis of SCLC upon follow-up.

1. Biomarkers in the peripheral blood of patients with LEMS, SCLC-LEMS, or SCLC only.

*Introduction*

Multiple biomarkers for LEMS have been studied in our cohort. We have previously identified SOX antibodies as specific serological marker for SCLC-LEMS.^24, 33^ Antibodies against the intracellular Hu protein are also found in SCLC patients with and without LEMS. Additionally, HLA-B8-DR3 was identified as a biomarker for LEMS without associated tumour.^14, 27^

*Hypothesis*

Multiple biomarkers including auto-antibodies and HLA type are present in LEMS and are associated with specific disease subgroups.

*Parameters*

We will test for Hu and SOX antibodies as well as HLA type.

*Future objectives:*

It is likely that in the future other biomarkers will become available. Currently, we are collaborating with prof. dr. [name] and dr. [name] (Dept. of Human Genetics) to search for new biomarkers. We expect that our study will identify patients with prolonged tumour survival or a favourable anti-tumour immune response. For these patients, genetic polymorphisms will be valuable for our understanding of the immune mechanism. The unfortunate poor survival of this patient group makes it impossible to ask for DNA samples to be taken later on during the study. Thus, because of the nature of this prospective study, combining detailed clinical and immunological data, we will store DNA for analysis in future studies.

1. Humoral and cellular aspects of the tumour immune response in SCLC-LEMS

*Introduction*

SCLC is a very immunogenic tumour, leading to more frequent occurrence of paraneoplastic syndromes compared to other tumours.^5^ The prolonged tumour survival associated with some of these paraneoplastic syndromes suggests a functional immune response against both tumour and healthy tissue. However, the pathways by which the immune system can control tumour growth remain unclear. We will study multiple possible pathways that could lead to a more tumour-rejecting type of immune response.

*Hypothesis*

- SCLC biopsies in LEMS patients show an increase in tumour infiltration by lymphocytes and macrophages.
- An anti-tumour effect of serum VGCC antibodies and related cellular immune responses can be detected *in vitro*.
- Specific T cells against tumour-related antigens, such as VGCC, are present in serum of LEMS patients.

*Parameters*

- Tumour infiltration of SCLC by lymphocytes and macrophages (+- LEMS)
- Anti-tumour effect of serum VGCC antibodies and related macrophage and adaptive response in vitro
- Presence of specific T cells against tumour-related antigens

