### Imaging studies

For patients with SCLC we will ask for permission to collect their previous lung imaging studies. This will allow us to compare size and distribution of the lung tumour for patients with and without LEMS. As for tumour tissue, we have collected clinical data of multiple SCLC-LEMS patients. For the same reasons stated in the previous paragraph, we will not obtain specific permission for obtaining imaging studies of patients who are already deceased. Instead we will request these imaging studies directly, stating this procedure is supported by the METC.

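### The SCLC-LEMS versus SCLC-only comparison of tumour size makes no allowance for LEMS-prompted detection, and tumour growth has no consistent timing, scale or treatment status

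*Combined protocol and SAP*

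**What the plan says.** All references are to the Dutch protocol in the combined document.

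- **Hypothesis (section 5.1, objective 1):** "Lung tumours in SCLC-LEMS patients are smaller on average and grow at a slower rate compared to tumours in SCLC patients without LEMS".
- **Timing.** The introduction to that objective says imaging will determine "tumour size and growth upon diagnosis in SCLC-LEMS patients compared to SCLC only". The endpoint beneath it reads "Tumour size and growth rate upon follow-up".
- **How SCLC-LEMS tumours are found (section 1):** "Diagnosis of LEMS usually precedes diagnosis of SCLC by several months, thus prompting vigorous tumour screening". The same section reports that "a SCLC can be found in 96% of SCLC-LEMS patients within a year of the diagnosis of LEMS", and that CT detected 92% of tumours against 51% for chest X-ray.
- **How the comparators enter (sections 4.1 and 7.2):** pulmonology refers patients diagnosed with SCLC, and they are included after pathological confirmation. No screening step is described.
- **Imaging (section 5.2.4):** previous lung scans are collected. "This will allow us to compare size and distribution of the lung tumour for patients with and without LEMS". Growth is not mentioned there.
- **Nodal disease (section 5.1):** "Lung tumours in LEMS are also frequently present in mediastinal lymph nodes only".
- **Analysis (section 6):** a database and software packages are named. There is no test, adjustment, matching or stratification.

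**The concern.** The two groups reach diagnosis by different routes. Most SCLC-LEMS tumours are looked for because a neurological disease has already appeared. As far as the protocol describes, the comparators enter only after their cancer has been diagnosed. A tumour found earlier in its course is smaller, whatever its biology. Section 5.1 introduces the hypothesis alongside prolonged survival and macrophage infiltration, so a positive result invites an immunological reading that the comparison cannot separate from early detection.

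Growth has a separate problem. The two statements of timing differ, and no scale, scan interval or treatment status is given. If some scans fall before treatment and others during it, the measured change mixes growth with response.

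**Working it through.** **No planned figure to reproduce.** The protocol gives no effect size, SD, alpha, power or sample size for this comparison. The 50 LEMS-negative SCLC patients in section 3 are named as controls for the immunological studies; using them as imaging controls below is an assumption.

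**Patients available.** Section 5.1 expects 4 to 6 LEMS patients a year, and section 1 puts SCLC at 50 to 60%. That gives 4 × 0.5 = 2.0 to 6 × 0.6 = 3.6 new SCLC-LEMS patients a year. About half of the existing 120 LEMS patients gives up to about 60 retrospective cases.

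**Size with identical biology.** Assume exponential growth, the same volume doubling time D in both groups, and a lead time L in SCLC-LEMS. Then

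diameter ratio = 2^(−L / 3D).

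| Lead L | D = 1 month | D = 2 months | D = 3 months |
| --- | --- | --- | --- |
| 3 months | 0.50 | 0.71 | 0.79 |
| 6 months | 0.25 | 0.50 | 0.63 |

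A 3-month lead makes diameters 1 − 0.79 = 21% to 1 − 0.50 = 50% smaller. At the mild end, L = 1 month and D = 120 days give a ratio of 0.94, or 6% smaller.

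**Chance of a significant false finding on size.** Compare log diameters, 20 SCLC-LEMS against 50 controls, two-sided 5%. Take D = 60 days and L = 3 months (91.2 days):

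- Log difference = ln 2 × 91.2 / (3 × 60) = 0.351.
- Log-SD 0.4 (assumed): SE = 0.4 × √(1/20 + 1/50) = 0.106, so power = Φ(0.351/0.106 − 1.96) = 0.91.
- Log-SD 0.6 (assumed): SE = 0.159, so power = 0.60.
- With 60 SCLC-LEMS patients the figures are 1.00 and 0.86.

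Over the full range examined with 20 SCLC-LEMS patients (D 30 to 120 days, L 1 to 6 months), the chance runs from 0.06 to 1.00.

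**Growth and lead time.** In mm per month, growth is diameter × ln 2 / (3D) × 30.4. With an assumed 50 mm diameter at the later detection and D = 60 days this is 5.85. After a 90-day lead the diameter is 50 × 2^(−90/180) = 35.4 mm and the rate is 4.14. Simulation with variable doubling times gave medians of 5.8 and 4.0. On a log or doubling-time scale, lead time alone gives no difference.

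**Growth and treatment.** Identical biology was simulated for 20 against 50 patients, with volume on treatment assumed to fall to one eighth over 3 months.

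| Share scanned on treatment: SCLC-LEMS / controls | Falsely slower in SCLC-LEMS | Falsely faster in SCLC-LEMS |
| --- | --- | --- |
| 80% / 80% | 5% | 1% |
| 80% / 50% | 68% | 0% |
| 50% / 80% | 0% | 59% |

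In absolute units, if everyone's diameter halves on treatment, a 90-day lead gives median changes of −17 mm in SCLC-LEMS and −25 mm in controls. That runs against the hypothesis.

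**The case against.** Much can be said for the plan. Objective 1 is descriptive, and the main objective is immune pathophysiology. The interval of several months runs from LEMS diagnosis to SCLC diagnosis; it is not the time gained over detection by symptoms, so the lead used above has no anchor in the documents. The protocol says that LEMS usually comes first, not always. These points limit the size of the problem. They do not remove it, because no section records or adjusts for the route to detection.

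A reader might infer several stronger claims that the documents do not support:

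- **Growth is measured after treatment starts.** No section says so. Section 5.1 also places growth at diagnosis, and section 5.2.4 collects earlier scans. The before-and-after-chemotherapy wording in section 5.2.5(g) concerns blood, and the pre-chemotherapy statement in section 5.2.3 concerns tissue. Scans have neither.
- **Treatment favours the hypothesis.** It can push either way, as the simulation shows.
- **Only LEMS patients have serial untreated scans.** Nothing in the documents indicates which group has them.
- **Node-only patients are scored as zero or dropped.** No such rule is written. The protocol raises nodal disease itself as a reason to study distribution. What is missing is a stated size measure.
- **This is the only explicit clinical hypothesis.** DELTA-P prediction has its own in section 5.1.

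Restricting the size comparison to SCLC-LEMS tumours not found by screening would also be a poor remedy. At 2.0 to 3.6 new cases a year, it would leave few patients and would select tumours by how they presented.

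**Conclusion.** The point on size stands on the protocol's own text: followed as written, the plan could report smaller tumours in SCLC-LEMS with no biological difference. The 21 to 50% figure illustrates a 3-month lead, a doubling time of 1 to 3 months and exponential growth, all assumed; the effect could be as small as 6% within the range examined.

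For growth, lead time alone produces a false difference only in absolute units. Beyond that, the defect is unreconciled timing and undefined treatment status, with bias possible in either direction. It does not follow that both halves of the hypothesis would be confirmed by artefact. Severity is moderate, since this is one component of one of four specific objectives, and the change is a cheap improvement.

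**What to change.** 1. Record mode of detection (LEMS-prompted screening, or tumour symptoms or SCLC known first) and the interval from LEMS to SCLC diagnosis.
2. Present the size comparison stratified by mode of detection. Do not interpret an overall difference as biological if it is confined to screen-detected cases.
3. Reconcile the two growth timings in section 5.1. Define growth on a log or doubling-time scale from scans made before any tumour treatment, and report later change separately as response.
4. Apply one size measure that includes nodal disease to both groups, and state which SCLC-only patients serve as imaging controls.
5. Where too few patients have the needed scans or detection modes, label the comparison descriptive.

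The cost is some extra data abstraction and measurement on scans already being collected, and smaller numbers in the strata and in the growth analysis.
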